**Methods/Design:**

In this population-based observational cohort study, the investigators identify patients at high risk of ALI using the prediction model applied within the first six hours of hospital admission. Using a validated system-wide electronic surveillance, Olmsted County patients at risk are followed until ALI, death or hospital discharge. Detailed in-hospital (second hit) exposures and meaningful short and long term outcomes (quality-adjusted survival) are compared between ALI cases and high risk controls matched by age, gender and probability of developing ALI. Time sensitive biospecimens are collected for collaborative research studies. Nested case control comparison of 500 patients who developed ALI with 500 matched controls will provide an adequate power to determine significant differences in common hospital exposures and outcomes between the two groups.

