## Background

Acute lung injury (ALI) and its more severe form Acute respiratory distress syndrome (ARDS) are common and devastating complications after acute illness or injury with high morbidity and mortality, long term decrease in quality of life, and enormous costs related to intensive care and rehabilitation [1]. ALI is an example of a critical care syndrome with limited treatment options once the condition is fully established. Despite improved understanding of the pathophysiology of ALI, the clinical impact has been limited to improvements in supportive treatment [2,3]. Surprisingly little research has been done on the prevention of ALI. Preclinical studies support a "two hit" model of development of ALI whereby different exposures modify the expression of ALI in susceptible host [4]. Preliminary data suggest that ALI is rarely present at the time of hospital admission but develops over a period of hours to days in subsets of patients with predisposing conditions such as pneumonia, sepsis, trauma, shock and corresponding medical and surgical interventions [5-12]. To this extent, ALI may be viewed as potentially preventable hospital complication similar to stress ulcer bleeding, venous thromboembolism or nosocomial infections. Previous clinical studies enrolled patients after ICU admission, often with already established ALI, beyond the window of meaningful mechanistic studies and potential prevention strategies [13-15]. Not surprisingly, many treatments targeting the mechanisms identified in preclinical studies have failed to improve patient outcomes despite compelling preclinical data [16-19]. It is likely that, inadequate and delayed recognition of patients at risk and the subsequent development of the full blown syndrome have obscured the therapeutic window. ALI usually develops during the first hours of ICU admission, and often is the very reason for ICU admission. On the other hand, the majority of patients with predisposing conditions never develop ALI and they may never been admitted to the ICU making the enrollment of unselected patients into ALI prevention studies neither feasible nor efficient [12,10]. A meaningful approach to ALI prevention therefore ought to be based on identifying patients at risk earlier than what is currently done (at the time of hospital admission, rather than ICU admission, Figure 1) [10].

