## Methods/Design

In this population based cohort study the investigators will identify patients at risk early in the course of the disease and *before *the development of ALI (at the time of hospital admission). Detailed in-hospital exposures, short and long term outcomes will be compared between patients at high risk who do and do not develop ALI. (Figure 2)

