### Inclusion Criteria

Olmsted County residents more than 18 years of age admitted to the two Mayo Clinic Rochester hospitals with one or more of the ALI predisposing conditions (sepsis, pneumonia, aspiration, pancreatitis, shock, high risk trauma, and high risk surgery). (Table 1) Exclusion criteria are listed in Table 2. Institutional review board has approved the study protocol.

**Table 1 T1:** Predisposing conditions and modifiers available before or within six hours after hospital admission used to calculate the lung injury prediction score (LIPS):[22].

*Risk factors*	Measurement	Definition
Pneumonia	Yes/No	Consensus Conference[24]
Sepsis	Yes/No, severe	SCCM-ACCP definition[25]
Pancreatitis	Yes/No	Practice guidelines in acute pancreatitis[26]
Aspiration (pre-admission)	Yes/No	Inhalation of food or gastric contents[27]
High risk trauma	Lung contusion, smoke inhalation, near-drowning, multiple bone, brain injury	From Derdak [28]
High risk surgery	Aortic vascular, spine, thoracic, acute abdomen, emergency	From Arozullah et al [29,30]
*Risk Modifiers*		
Alcohol use	Yes/No, amount (# of drinks a week)	More than 2 drinks per day or a history of alcohol-related illness or admission[31,32]
Smoking	Never/former/current/# of pack-years	Substance Abuse and Mental Health
Diabetes mellitus*	Yes/No	Diabetes care 2009[33]
Interstitial lung disease	Yes/No	ATS-ERS Consensus classification of IIP[34]
Chemotherapy	Yes/No	Custom, cancer chemotherapeutic drugs during the 6 months prior to hospitalization
Tachypnea (respiratory rate>30),		Based on the worst value during the first 6 hours
High inspired oxygen concentration (FIO2>0.35)		Based on the worst value during the first 6 hours
Hypoalbuminemia		Serum albumin <3.5 g/dL, the absence of measurement considered normal

*Only if sepsis

**Table 2 T2:** Exclusion criteria.

Exclusion Criteria	Justification
Acute lung injury or pulmonary edema already present at the time of hospital admission	Unable to assess for development of outcome of interest
Admitted for comfort or hospice care only	Missing predictor and outcome variables
Denied the use of medical records for research (~5%)	Self explanatory
Patients admitted for cardiac telemetry, coronary care unit, low risk elective surgeries, labor and delivery	Very low risk of outcome of interest
Children	Different risk factors and outcome
Hospital readmission	Complexity of analysis
Hospital transfer	Exposure to health care interventions

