### Validation of the primary outcome (ALI)

Primary outcome is the development of ALI at any time during the hospital stay. Trained investigators review each ARDS sniffer alert (see above) and confirm the presence or absence of ALI according to the standard definition based on the American-European consensus conference [21]. The absence of left atrial hypertension as the principal explanation for pulmonary edema is confirmed by integrated clinical evaluation based on the following:

• Echocardiography (E/E'<15, EF>45)

• Pulmonary artery occlusion pressure (PAOP) ≤ 18 cm H2O

• Central venous pressure (CVP < 15) cm H2O (higher cutoff in pulmonary hypertension)

• History of congestive heart failure/cardiogenic pulmonary edema

• Brain natriuretic peptide (BNP) <250 pg/mL (higher cutoff in renal failure)

• Response to preload reduction: brisk (hours) response to diuretics and/or positive pressure ventilation favors hydrostatic edema

This process yielded good interobserver agreement for differentiation between ALI and hydrostatic edema (Kappa value 0.83 in the most recent retrospective Olmsted county study)[10].

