### Statistical Analysis

An estimate for the probability of ALI development will be calculated for each patient based on the LIPS model. Because of subjective nature of clinical definitions used to identify the outcome of our study, it is necessary to assess interobserver variability. Interobserver agreement for ALI development will be assessed by calculating the Kappa statistic, using a threshold of 0.6 as an indication of acceptable interobserver agreement.

The calibration and discrimination of model will be assessed using the Hosmer-Lemeshow goodness-of-fit test and the receiver operating characteristic curve, respectively. An area under the ROC curve greater than 80% will be considered to be the evidence of good model discrimination. Using a LIPS cutpoint of 3.5 or more identified in the preliminary data, the comparison of the model prediction versus the actual event observed will be summarized by a simple 2 by 2 table reporting ALI propensity versus ALI development. Summary measures, based on the 2 by 2 table, will be reported: sensitivity, specificity, positive predictive value, negative predictive value, positive and negative likelihood ratios along with their 95% confidence intervals.

In a matched case-control design the associations suggested by preliminary clinical studies (Table 3) will be compared between ALI cases and high risk controls propensity matched by age, gender and the probability of ALI development at the time of hospital admission (LIPS, see above). Subpopulation analyses will be performed to determine what hospital exposures are associated with ALI in low/moderate ALI risk patients and what hospital exposures factors are associated with no ALI development in high ALI risk patients. The primary statistical endpoint is the development of ALI at any time during hospital stay. The matching is based on ALI risk at admission and the exposure period at risk. For example, if a hospitalized patient, who has an estimated propensity for developing ALI of 20% actually develops ALI 10 hours after hospital admission the exposures in matched control patient is only measured during the initial 10 hours after hospital admission. Paired statistics will be used for group comparisons. A conditional logistic regression model will be built in the case of baseline imbalances.

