The statistical endpoints for determining attributable burden of ALI development in patients at risk are unadjusted and quality adjusted survival after hospital admission. All patients will be followed until death or study conclusion, and patients who survive will be censored at the last date known to be alive. In addition, we will assess which hospital exposures, impact the long-term survival and quality-adjusted survival in both ALI patients and high risk controls. We will use Kaplan-Mayer survival curves to depict survival differences in these subgroups. In order to understand the impact of ALI on quality of life, we will compare the l quality of life measures between the ALI patients and controls, taking into account the correlations between serial (baseline and follow up) QOL measurements. We will carry out quality-adjusted life years (QALY) analyses to incorporate the QOL-related health state utility variables into the survival analysis. We will combine survival and quality of life using the time spent in specific "health state" (ventilator, ICU, hospital, nursing home, home) to describe the quality adjusted survival of ALI patients according to the following formula:

We expect that missing data will be minimized due to the error checking capability of our data entry system. We will handle missing data in a number of ways including complete case analysis and imputation via nearest neighbor, mean value, last value, and zero value carried forward approaches. Multiple approaches are used so that the sensitivity of results to alteration in imputational assumptions may be assessed.

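### Survival is counted from admission, and controls are not required to be alive, in hospital and ALI-free at the case's onset; if they need not be, the ALI effect on survival is understated

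*Protocol article*

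**What the plan says.** All places are in the protocol article.

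- **Time origin.** Statistical Analysis gives the burden endpoints as "unadjusted and quality adjusted survival after hospital admission". Follow-up runs to death or the end of the study. No index date, landmark or time-dependent ALI term is named.
- **When a patient becomes a case.** Validation of the primary outcome: "Primary outcome is the development of ALI at any time during the hospital stay". Table 2 excludes "Acute lung injury or pulmonary edema already present at the time of hospital admission", so no case is a case at time zero. Background states that "ALI is rarely present at the time of hospital admission but develops over a period of hours to days".
- **Groups compared.** Methods/Design compares exposures and outcomes between "patients at high risk who do and do not develop ALI". The abstract, which also covers outcomes, describes "high risk controls matched by age, gender and probability of developing ALI".
- **Time in the matching.** Statistical Analysis adds: "The matching is based on ALI risk at admission and the exposure period at risk". In its worked example, for a case with onset at 10 hours, "the exposures in matched control patient is only measured during the initial 10 hours after hospital admission". Identification of in-hospital exposures likewise uses the corresponding period in controls only to decide which exposures are analysed.
- **Planned effect.** Beside Figure 3: control median survival of about 2 years, risk of death raised by about 1.25 and 80% power, for 500 cases and 500 controls.

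**The concern.** When groups are defined by an event after time zero, the time from zero to that event is free of deaths in one group by construction. A high-risk patient who dies at hour 6 without ALI can enter the study only as a control. A patient who develops ALI at hour 48 brings 48 hours of guaranteed survival into the comparison. Unless each control must also have survived ALI-free to the case's onset hour, mortality attributable to ALI is understated.

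The same gap affects the exposure analysis. A control who died or went home before the case's onset hour has no data for the rest of the matched window, so cumulative doses and areas under the curve (Table 3) are lower for want of time rather than for want of exposure.

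Attributable burden is one of the three products named in the Conclusion and is meant to set priorities for prevention trials. The planned ratio, 1.25, is small enough for a modest attenuation to matter.

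**Working it through.** **1. The plan's own power figure.** Read 1.25 as a hazard ratio, with two-sided 0.05 (the 0.05 is stated for Figure 3 and carried over here).

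- Events needed (Schoenfeld): 4 × (1.960 + 0.842)² / (ln 1.25)² = 31.40 / 0.0498 ≈ 631. Freedman's formula gives 636.
- Events expected with exponential survival and 2.6 years for everyone: controls 500 × (1 − 2^−1.3) = 297; cases 500 × (1 − 2^−1.625) = 338; total 635.
- Power = Φ(√635/2 × ln 1.25 − 1.96) = Φ(0.85) = 80%.

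Power is 73.6% at 2 years of follow-up and 83.3% at 3 years. The stated 80% is therefore attainable, but it cannot be confirmed because no follow-up duration is given.

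**2. Effect of unrestricted controls.** Assumptions that are not in the document: 14-day control mortality of 2% to 20%, median onset of 0.5 to 4 days (exponential, within 14 days), 10% of patients susceptible, 2.6 years of follow-up. Control median survival is held at 2 years. The simulation had 1.5 million admissions per scenario, with ALI as a time-dependent event. Discharge was not modelled, so the part of the rule that concerns being in hospital was not tested.

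Estimated hazard ratio when the truth is 1.25, clock at admission, any never-ALI patient eligible as control:

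| 14-day mortality | onset 0.5 d | 1 d | 2 d | 4 d |
|---|---|---|---|---|
| 2% | 1.250 | 1.245 | 1.255 | 1.230 |
| 5% | 1.247 | 1.239 | 1.229 | 1.218 |
| 10% | 1.243 | 1.219 | 1.192 | 1.173 |
| 20% | 1.226 | 1.194 | 1.137 | 1.091 |

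Run-to-run error is about 0.005, so the entry above 1.25 is noise. When the truth is 1.00, the estimates run from 0.88 to 1.00.

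**3. Hand check at 10% mortality and 2-day onset.**

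- Daily hazard to day 14: −ln(0.9)/14 = 0.00753, a cumulative 0.1054.
- Daily hazard after day 14, for a 2-year median: (0.6931 − 0.1054)/716 = 0.000821.
- Mean onset is about 2.8 days, so cases skip about 0.0209 of the early hazard.
- Case-to-control ratio in the first 14 days: 1.25 × (0.1054 − 0.0209)/0.1054 ≈ 1.00. After that it is 1.25.
- Control mortality at 2.6 years (949 days): 1 − exp(−(0.1054 + 935 × 0.000821)) = 58%. The first 14 days hold 10/58 ≈ 17% of deaths.
- Weighted ratio: 0.17 × 1.00 + 0.83 × 1.25 ≈ 1.21, close to the simulated value. Twenty repeat runs of this scenario average 1.20.

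**4. Power at the attenuated effect, 635 events.**

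- At 1.19: Φ(12.60 × 0.1740 − 1.96) = Φ(0.23) ≈ 59%.
- At 1.20: Φ(12.60 × 0.1823 − 1.96) = Φ(0.34) ≈ 63%.
- At 1.09, the worst case tried: Φ(12.60 × 0.0862 − 1.96) = Φ(−0.87) ≈ 19%.

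**5. With eligible controls.** With controls alive at the case's onset and the clock started there, the estimates are 0.99 to 1.01 (truth 1.00) and 1.24 to 1.27 (truth 1.25), which is simulation noise. With the same controls and the clock left at admission, the values are essentially the same. Eligibility therefore does nearly all of the correction.

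**The case against.** The strongest reply is that the plan already matches on time at risk. The sentence "The matching is based on ALI risk at admission and the exposure period at risk" names the period as a matching basis, and the 10-hour case is offered as an example, not as the whole rule. A control who left at hour 4 has no natural 10-hour corresponding period. On that reading controls share the case's survival to onset and the bias essentially disappears, even with the clock at admission. A condensed article may also leave the matching algorithm to a fuller plan.

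Much of this stands, and it limits the point to an unstated rule. It does not close the point. Both places that explain the time alignment apply it to exposures only, the abstract's match factors leave it out, and the survival text does not refer to it. Validity therefore turns on a reading that the text does not fix.

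A reader might also infer that the design would make ALI look protective. The plan's own inputs do not support this. At a ratio of 1.25 with long follow-up, no scenario tried fell below 1. Estimates below 1 need a true effect near null, or a short horizon with late onset or high early mortality, and the plan names no short-horizon survival endpoint. Excluding comfort-care and hospice admissions (Table 2) also removes some of the earliest deaths.

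**Conclusion.** The point holds as a gap in the stated matching rule and time origin. If controls need not be alive and ALI-free at the case's onset, the survival effect of ALI is attenuated: a planned 1.25 becomes about 1.09 to 1.25, and a true null becomes 0.88 to 1.00. Power falls from 80% to about 59% to 63% in the middle scenario and to about 19% in the worst one. With onset within a day and early mortality of 5% or less, the loss is negligible. These sizes rest on assumed early mortality, onset times and 2.6 years of follow-up. The mechanism and its direction follow from the document alone.

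A reader might take the admission clock by itself to be the fault. It is not: once controls are eligible at onset, moving the clock changes the hazard ratio very little. The exposure-window problem is likewise one of eligibility only, and it was not quantified.

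**What to change.** - **Matching (Statistical Analysis).** State that each control must be alive, in hospital and ALI-free at the same elapsed time since admission as the matched case's onset.
- **Survival (Statistical Analysis, burden endpoints).** Start unadjusted and quality-adjusted survival for both members of the pair at that index time. Alternatively, model ALI as a time-dependent covariate. That model belongs in the whole at-risk cohort, because in the matched sample the cases' time before onset is free of deaths by selection.
- **Later ALI in controls.** Say whether a control may develop ALI after the index time. Allowing it is optional, since it changes the stated contrast between patients who do and do not develop ALI.

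**Cost.** A change to the matching query and the time origin, with no new data. The control pool will be somewhat smaller for late-onset cases. Deaths before the index time no longer count in the burden contrast, so they should be reported descriptively.

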### Attributable burden of ALI

To prioritize future ALI prevention strategies, we are planning to determine the attributable burden of ALI in the Olmsted County community by quantifying patient-centered outcomes attributable to this condition. The essential patient-centered outcomes (unadjusted and quality-adjusted survival, neurocognitive, neuropsychologic and neuromuscular complications, functional outcome, and quality of life) will be compared between patients who do and do not develop ALI. The instruments we have chosen to evaluate our patients are listed in Table 4. These instruments were selected to assess the key domains of patient centered outcomes without jeopardizing the ability and willingness of the patients to provide data. Specifically these instruments will give a general measure of Quality of life (QOL) (SF12), along with measures of physical, cognitive and psychological functioning and would provide a comprehensive picture of our patients' experience. Baseline (premorbid) functional status and QOL will be determined by in-hospital retrospective survey of the patients or their surrogates. After obtaining informed consent trained study coordinators establish if the patient is competent to complete the entire questionnaire by administering the mini mental test. If patient is deemed incompetent or too ill to complete the survey a surrogate will be identified to help fill the questionnaires. Follow-up contact information will be obtained and the patients or their surrogate who successfully complete the baseline survey will be contacted by telephone six month after index hospitalization.

**Table 4 T4:** Patient-reported outcome assessment.

Variable	Instrument	Time(s) of assessment
Quality of life	SF-12 health survey	1. In hospital retrospective assessment of pre morbid QOL 2. 6 month follow up
Physical function	Barthel Index	1. In hospital retrospective assessment of pre morbid QOL 2. 6 month follow up
Neuromuscular complications	Overall neuropathy limitations scale	1. In hospital retrospective assessment of pre morbid QOL 2. 6 month follow up
Neurocognitive complications	Folstein mini-mental status scale	1. In hospital retrospective assessment of pre morbid QOL 2. 6 month follow up
Neuropsychological complications	1. Post-Traumatic Stress Syndrome (PTSS-10) (only at 6 months) 2. Yale depression scale	1. In hospital retrospective assessment of pre morbid QOL 2. 6 month follow up

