### Strategies for subject retention

We selected survey instruments to minimize respondent burden. In preliminary testing, respondents completed the battery of tests in less than 15 minutes. At baseline the research assistant administer the questionnaire with the use of visual aids to help with answering the questions. When obtaining the consent, patients will be informed of the follow up survey and the same research assistant will contact the patients at six months. This will help in establishing a rapport and increasing the response rate at follow-up. The average retention rate for the surveys conducted by the QOL research team at our institution is in excess of 80%.

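### The listed single-value fills (mean, last value, zero) are unsuitable for the six-month survey outcomes: last value assumes a return to premorbid status, and the other two distort the standard error or the estimate

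*Protocol article*

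**What the plan says.** The Statistical Analysis section lists five ways of handling missing data: "complete case analysis and imputation via nearest neighbor, mean value, last value, and zero value carried forward approaches". It gives the reason: "Multiple approaches are used so that the sensitivity of results to alteration in imputational assumptions may be assessed". None is named as primary, and none is tied to a type of variable. The amount of missing data is expected to be small for a data-entry reason: "We expect that missing data will be minimized due to the error checking capability of our data entry system".

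Table 4 (Attributable burden of ALI) gives each instrument two assessment times: "1. In hospital retrospective assessment of pre morbid QOL 2. 6 month follow up". The exception is the PTSS-10, which is taken at six months only. The text above the table confirms what baseline means: "Baseline (premorbid) functional status and QOL will be determined by in-hospital retrospective survey of the patients or their surrogates". Patients or surrogates who completed that baseline survey are the ones telephoned at six months.

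Strategies for subject retention states: "The average retention rate for the surveys conducted by the QOL research team at our institution is in excess of 80" per cent. Sample size considerations plans the quality-of-life comparison on 100 ALI survivors and 100 controls, SD 10, with 80% power for a difference of 4.0 units.

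**The concern.** The article's reason for expecting few missing values does not cover the loss it foresees elsewhere. Range checks at data entry cannot make a discharged patient answer the telephone, and retention just above 80% means that up to about one survey in five could be missing.

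For those patients the listed fills behave as follows.

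- **Last value.** The only earlier score is the recalled premorbid one. Carrying it forward sets the patient's change to zero, which is to assume no lasting decline. That decline is what the burden analysis sets out to measure. For the PTSS-10 there is no earlier value to carry.
- **Mean value.** The filled scores add no spread but are counted as observed patients. What follows depends on whether the mean is taken by group or overall, and the article does not say.
- **Zero value.** A fixed constant enters each group in proportion to its missingness, so unequal response produces a difference by itself.

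At stake is the attributable-burden comparison of quality of life, function and quality-adjusted survival. Attributable burden is one of the three products named in the Conclusion.

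**Working it through.** **Inputs from the article:** n = 100 per group, SD = 10, difference 4.0, power 80% (Sample size considerations); false positive rate 0.05 (Figure 3 legend, given for the case-control comparison); retention above 80%.

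**Assumed:** two-sided 0.05 also for quality of life; missing fraction m = 20%, with 10% and 30% as the range; mean score 40 to 50; an unequal split of 25% against 15% missing. Non-responders are taken to have the same true scores as responders, so any bias below comes from the fill alone.

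**1. The article's own figure.** SE = 10 × √(2/100) = 1.414, and 4.0/1.414 = 2.83. Power is 80.4% (t test) or 80.7% (normal approximation). The stated 80% is reproduced.

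**2. Complete case as comparator.** With 20% lost, 80 per group remain: SE = 10 × √(2/80) = 1.581, and power is 71.0% (normal 71.6%). At 10% lost it is 76%; at 30%, 65%.

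**3. Last value.** With equal premorbid means and equal missingness, the expected difference is (1 − m) × 4.0. Power is for n = 100 per group, with the SD kept at 10.

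| m | Estimate | Power |
|---|---|---|
| 10% | 0.9 × 4.0 = 3.6 | 72% |
| 20% | 0.8 × 4.0 = 3.2 | 61% (t test 61.5%, normal 61.9%) |
| 30% | 0.7 × 4.0 = 2.8 | 50% (normal 51%) |

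At 20% missing, about 10 points of power are lost relative to complete case; the rest of the fall from 80% comes from the missing data themselves. If missingness is unequal the bias can grow. With assumed declines of 8 units in cases and 4 in controls, and 25% against 15% missing, the estimate is 0.75 × 8 − 0.85 × 4 = 6.0 − 3.4 = 2.6.

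**4. Mean value, filled by group.** The reported SD is 10 × √(79/99) = 8.93, so the reported SE is 8.93 × √(2/100) = 1.26. The true SE is 1.58, and the ratio is 0.80. Type I error = 2 × [1 − Φ(1.96 × 0.80)] ≈ 12% (11.7% from the unrounded ratio, 11.9% by simulation with 40,000 runs). It is 8% at m = 10% and 17% at m = 30%.

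**5. Mean value, filled with the overall mean.** The estimate shrinks to 0.8 × 4.0 = 3.2, but its reported SE shrinks with it. By simulation (40,000 runs, m = 20%) type I error is about 5% and power about 71%. The test keeps its size; the estimate is biased.

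**6. Zero value.** With no true difference and 25% against 15% missing, the expected difference is mean × (0.75 − 0.85). For a mean of 40 this is −4.0; for a mean of 50, −5.0. These sizes follow wholly from the assumed split and mean. The article supports the direction of the argument, not a particular size.

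**The case against.** **The fills are offered as a sensitivity exercise, alongside complete case and nearest neighbor.** This is true, and nothing says that last value or zero will carry the conclusion. A reader might infer that the reported burden will rest on them; the text does not support that. But the stated purpose is met only if the spread of results says something about plausible missing-data assumptions. Here part of the spread reflects an understated standard error or an arbitrary constant.

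**The sentence is study-wide and does not name the survey.** This is also true. For serial ventilator readings or unrecorded drug doses, last value or zero may be a natural reading. Applying the sentence to the six-month outcomes is an inference, but a fair one, since that is where the article foresees losses. The same section also plans a quality-of-life comparison that allows for baseline and follow-up correlation, which is close to what is recommended here.

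**A condensed article may leave the choice of primary method to a full plan.** That is accepted: the missing primary method would not be a point by itself. The fills, however, are stated.

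**Stronger readings fail.** One might say that the burden could be erased, but last value leaves 3.2 of 4.0. One might say that no departure from missing at random is examined, but last value and zero are such departures, though crude. One might call zero the worst possible score, but the article gives no score range or direction for any instrument. A 12% type I error applies to group-mean fill only.

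**The 20% is a ceiling,** and the target of 100 per group may mean completers. Both limit the size of the effect, not its direction.

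**Conclusion.** The point holds for the six-month survey outcomes and the burden analyses built on them. The article commits to fills that, on its own assessment schedule, give a biased estimate (last value, overall mean, zero) or an overconfident one (group mean), and it gives no rule for where each applies. Last value is the clearest case, because its meaning follows directly from Table 4.

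The effect is moderate. At 20% missing, attenuation is one fifth of the true difference and the power cost against complete case is about 10 points; both are smaller if retention is better. The figures rest on the assumed missing fractions and a two-sided 0.05 level. Those for last value also need balanced premorbid scores and equal missingness, and those for zero fill need the assumed split and mean. ALI development (the primary endpoint), the LIPS validation and unadjusted survival do not depend on survey response.

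**What to change.** For six-month survey outcomes among survivors:

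- **Primary analysis:** a likelihood-based repeated-measures model, which is compatible with the serial-correlation analysis already planned, or multiple imputation using ALI status, premorbid score, respondent type (patient or surrogate), age and LIPS.
- **Sensitivity analyses:** keep complete case, and add a delta-adjusted analysis in which non-responders' scores are shifted by stated amounts that may differ between ALI patients and controls.
- **Remove** mean, last-value and zero fill for living non-responders. Keep zero only as the utility of death in the QALY analysis.
- **State** which of the remaining methods applies to which type of variable, so that fills meant for charted exposures are not carried over to the survey.

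The cost is revised wording, modest programming and possibly wider intervals. No new data are needed.
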